#### Primary outcome measurement

2.8.1

The primary outcome will be assessed using PSQI, a self-rating questionnaire designed to assess overall sleep quality. It includes 19 self-rating items and 5 other-rating items. It evaluates sleep quality according to the following 7 aspects over the past month: sleep duration, sleep efficiency, daytime dysfunction, delays in falling asleep, use of medications to sleep, sleep disorders, and overall sleep quality. Each aspect is rated 0 to 3 points, and the accumulated scores of the 7 aspects are 0 to 21 points. The higher score indicates poorer sleep quality. The reliability and validity of the Chinese version have been verified.^[11]^ The PSQI will be evaluated at baseline, during treatment period (at 4, 8, and 12 weeks) and follow-up period (at 1, 3, and 6 months).

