### Withdrawal criteria

2.11

The patients presenting the following conditions will be withdrawn from this study:

occurring serious adverse reactions so as to be inappropriate to continue the study;occurring severe complications or condition deterioration so as to need emergency measures;not following the prescribed treatment or without complete data so as to affect the efficiency of evaluation.

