### Sample size

2.12

PSQI scores after the end of acupuncture are taken as the sample size calculation index. The statistical significance level is set as 0.05, and 80% is taken as the statistical power. A previous study showed the PSQI score of patients with perimenopausal insomnia is 8.62 ± 2.93 in the acupuncture group and 14.76 ± 3.35 in the sham acupuncture group.^[8]^ According to this, the following formula is used to calculate the estimated sample size: N = 2[(t_α/2_ + t_β_)S/δ]^2^. The combined standard deviation is assumed as 1.5, and δ is 0.5 times of the standard deviation. β is 0.8, and α is 0.05. Considering the dropout rate of 20%, at least 79 cases will be required in each group. Therefore, we need to recruit a total of 158 patients for this randomized controlled trials (RCT).

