### Statistical analysis

2.13

The statistical analysts will be blind to the patients’ group allocation. All data, including data of the withdrawing patients during the trial, will be analyzed based on intention-to-treat. Two different researchers will participate in the data entry, and all data are entered twice to guarantee the accuracy. The statistical analysis will be performed using SPSS 24.0 software (IBM, Armonk, NY, USA). The measurement data will be expressed as mean ± standard deviation or median and separately compared using *t* test and Wilcoxon rank-sum test. The count data will be shown as number and percentage, and compared using chi-squared or Fisher exact test. The change of PSQI score between the 2 groups at different time points will be compared by repeated-measures analyses of variance. The difference before and after treatment in each group will be determined using paired *t* test. All statistical tests are 2-tailed, with *P* values ≤.05 as statistical significance.

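### Repeated-measures ANOVA, as named and with no imputation step stated, drops every patient who misses a PSQI visit, which conflicts with the promised intention-to-treat analysis of all data.

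*Protocol article*

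**What the plan says.** Section 2.13 of the protocol article sets the analysis set: "All data, including data of the withdrawing patients during the trial, will be analyzed based on intention-to-treat". The same paragraph names the software, "The statistical analysis will be performed using SPSS 24.0 software", and the one longitudinal method for the primary outcome: "The change of PSQI score between the 2 groups at different time points will be compared by repeated-measures analyses of variance". It also lists t tests or Wilcoxon tests for measurement data in general, and labels no test as primary. No imputation or other treatment of missing values is stated.

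Three other sections bear on this:

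- Section 2.8.1 and Table 1 schedule PSQI at seven time points: baseline, weeks 4, 8 and 12, and months 1, 3 and 6 of follow-up.
- The Sample size section (2.12) expects losses: "Considering the dropout rate of 20%, at least 79 cases will be required in each group".
- The Withdrawal criteria (2.11) remove patients for, among other reasons, "not following the prescribed treatment or without complete data so as to affect the efficiency of evaluation".

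**The concern.** Classical repeated-measures ANOVA (the GLM Repeated Measures procedure in SPSS) works on one complete row per patient and deletes any row with a gap. A patient with a valid week-12 PSQI who misses only month 6 contributes nothing. The withdrawn patients whom section 2.13 says will be analysed are the ones this procedure leaves out.

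This goes beyond a detail left to a fuller document. The article fixes both an analysis set and a method, and the method as named does not deliver the set. What remains is a comparison of completers, a group formed after randomisation. Section 2.11 adds to the problem, because non-adherence and incomplete data may themselves be related to treatment or to sleep outcome. At stake is whether the PSQI comparison over time keeps the protection of randomisation.

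**Working it through.** **1. The plan's own sample size.** Inputs from section 2.12: SD 1.5, difference 0.5 × 1.5 = 0.75, two-sided alpha 0.05, power 80% (the value 0.8 given there for β is evidently the power).

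n per group = 2 × [(1.96 + 0.8416) × 1.5 / 0.75]² = 62.8, rounded up to 63. Allowing for 20% dropout: 63 / 0.80 = 78.75, rounded up to 79 per group and 158 in total. The stated figure reproduces.

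**2. Patients left out by a complete-case ANOVA at 20% dropout.** This takes the 20% as total loss over treatment and follow-up, with no other missing visit.

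- Excluded: 158 × 0.20 = 31.6, about 32 patients.
- Analysed: 79 × 0.80 = 63.2 per group.
- Power ≈ Φ(0.75 / (1.5 × √(2/63.2)) − 1.96) = Φ(0.85) ≈ 80%.

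The inflation therefore does its job for power. The same formula at 79 per group gives 88%. That is the ceiling for a method that keeps everyone, reached only if no information is lost.

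**3. Intermittent missed visits (assumption, not in the document).** Suppose each of the six post-baseline visits is also missed independently with probability p. Complete cases per group = 79 × 0.80 × (1 − p)⁶.

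| p per visit | Complete cases per group | Excluded of 158 | Power |
|---|---|---|---|
| 0 | 63.2 | 31.6 | 80% |
| 2% | 56.0 | 46 | 75% |
| 5% | 46.5 | 65 | 67% |
| 10% | 33.6 | 91 | 54% |

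**4. Bias among completers (illustration).** The simulation used the plan's SD of 1.5 and a true difference of 0.75 at every post-baseline visit, with 100,000 patients per arm. Assumptions not in the document: equal correlation of 0.6 between visits, and a chance of dropping out before each visit that is either constant or depends on the previous PSQI. The quantity is the week-12 group difference among patients with all visits.

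| Dropout mechanism | Dropout, sham / acupuncture | Completers' difference (true 0.75) |
|---|---|---|
| Completely random | 20% / 20% | 0.74 |
| High scorers leave, both arms | 25% / 19% | 0.70 |
| High scorers leave sham, low scorers leave acupuncture | 25% / 33% | 0.22 |

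The first row agrees with no bias within simulation error: the standard error is about 1.5 × √(2/79,900) = 0.0075. The second row is (0.75 − 0.70)/0.75, about 7% low. The third is (0.75 − 0.22)/0.75, about 71% low, and is a deliberately extreme case. A milder case at the same SD and difference, with dropout depending on PSQI in the sham arm only, gave about 0.66, or (0.75 − 0.66)/0.75 = 12% low.

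**The case against.** The strongest reply is that section 2.13 gives a principle and a test, and the step between them (how gaps are filled) is commonly left to an analysis plan that is not shown. Imputation followed by ANOVA would satisfy both sentences, and so would a mixed model loosely called repeated-measures ANOVA. This stands to the extent that a reader should not infer that the plan is incapable of an intention-to-treat analysis. It does not remove the point: the article commits to a named method that, taken at its word, excludes patients the same paragraph includes.

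Other parts of the reply also stand:

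- **Primary test.** No test is labelled primary, and section 2.12 sizes the trial on PSQI after acupuncture ends with a two-means formula. A week-12 t test would keep a patient who misses only month 6. The loss of about 32 patients applies to a single model holding all seven visits, which is the natural reading of the sentence but still a reading.
- **Power.** A reader might infer that dropout leaves the trial underpowered. Step 2 shows otherwise; a shortfall needs the further missed visits assumed in step 3.
- **Bias.** A reader might attach one percentage to it. The document gives no dropout mechanism, and patients are to be blinded, so nothing in it points to reasons that differ by arm. The range in step 4 is as far as the calculation goes.
- **Missing completely at random.** It is too strong to say that completers are valid only under this condition. Dropout that depends on assigned group alone, for example, need not bias the contrast.

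**Conclusion.** The conflict between the intention-to-treat statement and the named method is real and concerns the primary outcome. With all seven visits in one model and no imputation, about 32 of 158 patients are excluded at the planned dropout. Power then stays at about 80%, so the harm lies in giving up the randomised comparison and in possible bias. That bias is negligible to small when dropout is random or similarly related to PSQI in both arms, and can be material when its reasons differ by arm; how large cannot be settled from the document. The conclusion assumes that the method is applied as named. A stated imputation step would resolve it.

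**What to change.** In section 2.13, replace the repeated-measures ANOVA with a likelihood-based mixed model for repeated measures (MIXED in SPSS 24). It should use every observed PSQI value of all randomised patients, with effects for group, visit and group by visit. Baseline can be part of the response vector or a covariate. The first choice keeps patients who have no later value in the model, and since a PSQI score above 5 is an entry criterion, every randomised patient should have a baseline score. Report the week-12 group contrast with its 95% CI. The model is valid under missing at random. Multiple imputation before the ANOVA, if specified in the text, is an acceptable alternative. Keep the completers analysis as a sensitivity analysis.

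Reconcile section 2.11 with the intention-to-treat statement: say that the PSQI data of patients withdrawn for non-adherence or incomplete data stay in the analysis, and whether their PSQI assessments continue. No model recovers values that were never collected.

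The change of method costs wording only, with the same data and software. If assessments after withdrawal are not already planned, collecting them would add some follow-up effort. The change should be made before unblinding.

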### Inclusion criteria

2.3

The patients should meet all the following criteria:

age between 18 and 75 years;meeting the diagnostic criteria of hypertension (systolic blood pressure 140-180 mm Hg and/or diastolic blood pressure >90 mm Hg);insomnia diagnosed in accordance with the International Classification of Sleep Disorders^[10]^;Pittsburgh Sleep Quality Index (PSQI) score >5;not receiving acupuncture for at least 1 year;agreeing to participate in this clinical study and signed the informed consent.

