## Discussion

3

Hypertension patients usually suffer from insomnia, leading to a poor quality of life.^[2,3]^ Moreover, insomnia further increases the risk of cardiovascular disease, especially hypertension.^[4]^ To improve the insomnia of hypertension patients, the proper treatment needs to explore. Acupuncture has been practiced in China more than 2000 years and has become widely applied in western countries in recent years.^[16,17]^ The current studies have showed that acupuncture can be used to relieve primary, perimenopausal, and cancer-related insomnia symptoms,^[18–20]^ but the effect on the insomnia of hypertension patients has not been determined. This randomized, double-blind and placebo-controlled trial aims to assess the effect of acupuncture in hypertension patients suffering from insomnia, which may provide high-quality clinical evidence for the treatment of acupuncture in the insomnia of hypertension patients.

Insomnia is mainly a subjective feeling, and the PSQI and the ISI used to evaluate sleep quality and insomnia severity are both scored based on patients’ subjectivity.^[11,12]^ The SAS and SDA questionnaires used to evaluate anxiety and depression are still subjective scores from insomnia patients and exist uncertainties.^[13,14]^ The controversies existing in the study on the efficacy of acupuncture are mainly based on the following points. First, either researcher or patient will appear psychological effect (placebo effect), which may cause deviation to the results. Second, the efficacy of acupuncture does not always depend on the specific acupoints, and the sham acupuncture intervention are suitable for the acupoints unrelated to sleep physiology.^[21]^ A systematic review from Yang et al^[22]^ reported that acupuncture showed a greater short-term hypotensive effect than non-sham acupuncture in controlled trials, which probably reflected a bias that the acupuncture showed no true hypotensive effect. Therefore, Yang et al^[22]^ recommended that future RCTs must adopted sham acupuncture as control to decrease the bias. Our study uses a strict RCT with double-blind method and sham acupuncture as control, which may decrease the bias in a larger extent and reflect the true effect of acupuncture. In addition, the wrist-worn sleep monitor (actigraphy) is applied to detect the sleep quality, which can objectively and accurately evaluate the therapeutic effect of acupuncture.

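### Alongside its between-arm tests, Section 2.13 plans paired t tests within each arm at the same P ≤ .05 threshold, not labelled descriptive, and these do not estimate acupuncture against sham

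*Protocol article*

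**What the plan says.** Section 2.13 (Statistical analysis) lists three kinds of test for continuous outcomes:

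- For continuous data in general: "The measurement data will be expressed as mean ± standard deviation or median and separately compared using" a t test or a Wilcoxon rank-sum test.
- For the primary outcome: "The change of PSQI score between the 2 groups at different time points will be compared by repeated-measures analyses of variance".
- For before-after change: "The difference before and after treatment in each group will be determined using paired" t test. No outcome is named, so this sentence covers the primary and the secondary outcomes alike.

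One closing rule applies to all of them: "All statistical tests are 2-tailed", with P ≤ .05 as the threshold. Nothing marks the paired tests as descriptive or supportive.

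The abstract and Table 1 place the secondary outcomes at baseline and week 12 only. Section 2.8.2 allows estazolam during the trial, and no arm is excepted. Section 2.3 requires "Pittsburgh Sleep Quality Index (PSQI) score >5" and raised blood pressure at entry. The Discussion concedes that "either researcher or patient will appear psychological effect (placebo effect), which may cause deviation to the results" and gives this as part of the case for a sham control.

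**The concern.** The trial asks whether acupuncture does better than sham. A paired test within one arm asks whether that arm's mean moved from its starting value. Anything that moves an arm counts as movement: needle-specific effect, placebo response, rescue medication, the passage of time, or regression to the mean. The sham arm is there to subtract these, and a within-arm test does not subtract them.

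Two misleading patterns can follow when the arms improve equally. One arm may cross P ≤ .05 and the other not, which invites the conclusion that acupuncture worked and sham did not. Or both may cross it, which invites the conclusion that acupuncture was effective, with a P value in support. Neither pattern is evidence on acupuncture against sham.

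The exposure is greatest for the secondary outcomes. The repeated-measures ANOVA is named for PSQI only. For the sleep parameters, blood pressure, SAS and SDS, the paired test is the only one expressly tied to before-after change, and blood pressure reduction is itself defined as a change.

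**Working it through.** **Inputs from the protocol (Section 2.12).** "The statistical significance level is set as 0.05, and 80% is taken as the statistical power". "The combined standard deviation is assumed as 1.5, and δ is 0.5 times of the standard deviation", so δ = 0.5 × 1.5 = 0.75 points. Dropout is 20%. The cited perimenopausal study had SDs of 2.93 and 3.35.

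**Input not in the protocol.** The correlation ρ between baseline and week-12 scores is assumed to be 0.5, with a range of 0.3 to 0.7.

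**Step 1: the protocol's own figure.** With normal quantiles, n = 2 × [(1.960 + 0.842) / 0.5]² = 62.8, so 63 evaluable per arm. Then 63 / 0.8 = 78.75, rounded up to 79 per arm and 158 in total. The stated sample size reproduces, and 63 per arm is used below.

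**Step 2: a second SD.** Pooled from the cited study: √[(2.93² + 3.35²) / 2] = 3.147, about twice the protocol's 1.5. Both are carried forward.

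**Step 3: power of one paired test.** SD of change = SD × √[2(1 − ρ)], which equals the SD itself at ρ = 0.5. For a true mean fall m, the noncentrality is m × √63 / (SD of change), and the two-sided critical value on 62 degrees of freedom is 1.999. Call the resulting power p.

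**Step 4: equal true change, so no treatment effect.** The arms are independent, so P(exactly one significant) = 2p(1 − p) and P(both significant) = p².

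Results at ρ = 0.5:

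| SD | Common fall (points) | p | Exactly one arm | Both arms |
|---|---|---|---|---|
| 1.5 | 0 | 0.050 | 9.5% | 0.3% |
| 1.5 | 0.25 | 0.256 | 38% | 7% |
| 1.5 | 0.375 | 0.497 | 50% | 25% |
| 1.5 | 0.5 | 0.740 | 38% | 55% |
| 1.5 | 0.75 | 0.974 | 5% | 95% |
| 1.5 | 1.0 | 0.999 | 0.1% | 99.9% |
| 3.147 | 0.75 | 0.461 | 50% | 21% |
| 3.147 | 1.0 | 0.700 | 42% | 49% |
| 3.147 | 1.5 | 0.961 | 7% | 92% |
| 3.147 | 2.0 | 0.999 | 0.3% | 99.7% |

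The function 2p(1 − p) cannot exceed 50%, which it reaches at p = 0.5. Here that is a common change of about a quarter of the SD of change.

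**Step 5: sensitivity to ρ.** For ρ from 0.3 to 0.7, the 42% entry runs from 49% down to 19%. The 5% entry at 0.75 points with SD 1.5 runs from 16% down to 0.2%.

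**Step 6: the between-arm test in the same setting.** In 40,000 simulated trials (SD 1.5, ρ = 0.5, 63 per arm, equal true change), the two-sample t test on change was significant in 5.1% of trials at 0.375 points and in 4.9% at 0.75 points, so it keeps its nominal error.

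**The case against.** The strongest reply is that the paired tests are extras. The sentence just before them plans a between-group comparison of PSQI change, and the sample size is built on a two-group difference. The t and rank-sum tests most naturally compare the two arms, since the rank-sum test is for independent samples and the paired test is listed apart. Week-12 secondary outcomes therefore have a valid randomised comparison even though no test of their change between arms is spelled out. All of this stands. A reader might infer from the paired-test sentence that the randomised comparison is discarded, or that efficacy will be judged by setting one arm's P value against the other's. The protocol says neither.

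The second reply concerns size. The 42% is one point on a curve from about 0 to 50%, and it lies near the peak. It also uses an SD of about 3.15, where the protocol assumes 1.5. This stands too, and the figure should be read only with its range. If the placebo response is large, significance in one arm only becomes rare and significance in both becomes the rule. That changes which wrong conclusion is invited, but the test is still uninformative about acupuncture against sham.

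Third, regression to the mean through the PSQI entry limit is plausible but not shown. No baseline PSQI is given. If the cited sham-arm value of 14.76 ± 3.35 resembled untreated patients (an assumption), the cut-off of 5 would lie (14.76 − 5) / 3.35 = 2.9 SD below the mean and would exclude almost nobody. The point does not depend on it: placebo response and estazolam use are enough.

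Finally, labelling may be left to an analysis plan that is not shown. That would excuse silence. Here the protocol positively states the tests and puts them under the common significance rule.

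**Conclusion.** The point holds as a limited one. Section 2.13 plans within-arm hypothesis tests on the same footing as the between-arm tests, and they cannot address acupuncture against sham. The primary comparison is not replaced, and its error rate is unaffected. What is at risk is the interpretation of supplementary P values, chiefly for the secondary outcomes.

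With 63 evaluable per arm and no difference between arms, significance in exactly one arm has a probability between about 0 and 50%. Where it falls depends on the common change, on the SD and on a correlation that the protocol does not give. With larger common falls, significance in both arms is the expected result. The figures assume normally distributed changes and equal true change in both arms. The change is worth making because it costs almost nothing.

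**What to change.** In Section 2.13, drop the paired t tests as hypothesis tests. Report the mean change within each arm with its 95% CI, labelled as description only and without a P value. State that every efficacy conclusion, for PSQI and for the secondary outcomes, rests on the between-arm difference adjusted for the baseline value: ANCOVA at week 12, or a baseline term in the repeated-measures model for PSQI.

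The descriptive label alone would cure the paired tests. The baseline adjustment goes further, and supplies the between-arm test of change that the text does not spell out for the secondary outcomes.

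Cost: a change of wording, best made before unblinding. Table 1 already schedules baseline measurement of the primary and secondary outcomes, so no new data are needed and the sample size does not change. The only loss is the within-arm P values.

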## Discussion

3

Hypertension patients usually suffer from insomnia, leading to a poor quality of life.^[2,3]^ Moreover, insomnia further increases the risk of cardiovascular disease, especially hypertension.^[4]^ To improve the insomnia of hypertension patients, the proper treatment needs to explore. Acupuncture has been practiced in China more than 2000 years and has become widely applied in western countries in recent years.^[16,17]^ The current studies have showed that acupuncture can be used to relieve primary, perimenopausal, and cancer-related insomnia symptoms,^[18–20]^ but the effect on the insomnia of hypertension patients has not been determined. This randomized, double-blind and placebo-controlled trial aims to assess the effect of acupuncture in hypertension patients suffering from insomnia, which may provide high-quality clinical evidence for the treatment of acupuncture in the insomnia of hypertension patients.

Insomnia is mainly a subjective feeling, and the PSQI and the ISI used to evaluate sleep quality and insomnia severity are both scored based on patients’ subjectivity.^[11,12]^ The SAS and SDA questionnaires used to evaluate anxiety and depression are still subjective scores from insomnia patients and exist uncertainties.^[13,14]^ The controversies existing in the study on the efficacy of acupuncture are mainly based on the following points. First, either researcher or patient will appear psychological effect (placebo effect), which may cause deviation to the results. Second, the efficacy of acupuncture does not always depend on the specific acupoints, and the sham acupuncture intervention are suitable for the acupoints unrelated to sleep physiology.^[21]^ A systematic review from Yang et al^[22]^ reported that acupuncture showed a greater short-term hypotensive effect than non-sham acupuncture in controlled trials, which probably reflected a bias that the acupuncture showed no true hypotensive effect. Therefore, Yang et al^[22]^ recommended that future RCTs must adopted sham acupuncture as control to decrease the bias. Our study uses a strict RCT with double-blind method and sham acupuncture as control, which may decrease the bias in a larger extent and reflect the true effect of acupuncture. In addition, the wrist-worn sleep monitor (actigraphy) is applied to detect the sleep quality, which can objectively and accurately evaluate the therapeutic effect of acupuncture.

Our protocol provides a standardized process and we will follow each step of this protocol to conduct the subsequent clinical study. We expect that this trial will generate strong clinical evidence for the efficiency of acupuncture in hypertension patients’ insomnia management.
